## Abstract

**Background:**

People living with HIV (PLHIV) have to take lifelong antiretroviral treatment, which is often challenging. Young people living with HIV (YPLHIV) have the lowest viral load suppression rates in Malawi and globally, mostly due to poor treatment adherence. This is a result of complex interactions of multiple factors unique to this demographic group. The use of digital health interventions, such as real-time medication monitor (RTMM)-based digital adherence tools (DATs), could improve ART adherence in YPLHIV and subsequently improve viral load suppression which in turn could lead to reduced HIV-associated morbidity and mortality.

**Aim:**

To provide the evidence base for a digital adherence intervention to improve treatment outcomes in YPLHIV on ART.

**Objectives:**

1. The primary objective is to determine the efficacy of a customised DAT compared to the standard of care in improving ART adherence in YPLHIV.

2. The secondary objective is to determine the efficacy of the customised DAT compared to the standard of care in improving viral load suppression in YPLHIV.

**Methodology:**

This will be a parallel open-label randomised control controlled two-arm trial in which non-adherent YPLHIV in selected ART facilities in Blantyre will be randomised in a 1:1 ratio to a customised DAT and standard care arms and followed up for 9 months. The primary outcome is the proportion adherent at 9 months (> = 95% by pill count), and the secondary outcome is the proportion with viral load suppressed at 9 months (< 200 copies/ml).

**Discussion:**

There is a paucity of good quality evidence on effective digital health interventions to improve ART adherence and viral load suppression in YPLHIV globally and particularly in HIV high-burden settings like Malawi. This study will provide good-quality evidence on the effectiveness of a customised DAT in improving ART adherence and viral load suppression in this important demographic.

**Trial registration:**

The trial has been registered in the Pan African Clinical Trials Registry number: PACTR202303867267716 on 23 March 2023 and can be accessed through the following URL: https://pactr.samrc.ac.za/TrialDisplay.aspx?TrialID=25424. All items from the WHO Trial Registration Data Set are described in this manuscript.

**Supplementary Information:**

The online version contains supplementary material available at 10.1186/s13063-023-07496-6.

## Background

As of 2021, approximately 38.4 million people were living with HIV/AIDS (PLHIV) worldwide, of whom 28.7 million had access to antiretroviral therapy (ART) [1]. According to global estimates of 2021, about 3,300,000 young people (15–24 years of age) were living with HIV (YPLHIV), representing 8.6% of global HIV positives [1].

In Malawi, as of 2021, it was estimated that there were approximately 990,000 PLHIV, representing a population prevalence of 8.9% [1]. Furthermore, there were approximately 100,000 YPLHIV, a proportion of about 10% of PLHIV in Malawi [1]. Additionally, HIV prevalence in young people was estimated to be 2.5%, much higher than the global prevalence of 0.3% [1]. Going further, HIV incidence in young people was estimated to be 1.69 per 1000, much higher than the global estimate of 0.34 per 1000 [1]. In terms of HIV-related deaths in Malawi, as of 2021, it was estimated that YPLHIV contributed to approximately 1400 deaths out of a total of 7900 deaths, further emphasising the need to improve prevention and treatment interventions in this demographic [1].

The scale-up of ART has led to improved treatment outcomes in PLHIV. Early case detection, rapid ART initiation, and support of treatment adherence are the most important interventions reducing associated morbidity and mortality [2]. However, multiple studies have demonstrated significant gaps across the HIV treatment cascade in YPLHIV, resulting in less-than-ideal outcomes regarding linkage and retention in care and viral load suppression [2].

Viral load suppression is consistently lower in YPLHIV compared to other age groups. A cross-sectional study conducted in 2016 in southern Malawi on virological non-suppression in YPLHIV estimated that approximately 39% of YPLHIV were virally non-suppressed [3]. Furthermore, multiple Population-Based HIV Impact Assessments (PHIAs) in sub-Saharan Africa have backed this trend. For example, results from the Malawi Population-Based HIV Impact Assessment of 2020 showed that YPLHIV had a much lower viral load suppression prevalence as compared to other age groups; males had a viral load suppression prevalence of 75%, and females had a viral load suppression prevalence of 73.2% as compared to the national average of 88.3% [4].

Suboptimal adherence to an ART regimen is associated with a greater risk of developing resistance to antiretroviral agents and increases the risk of HIV-related morbidity and mortality and progression to AIDS [5]. Therefore, recognising the importance of ART adherence, UNAIDS recommends an adherence target of >  = 90% to combat HIV infections globally, while other studies recommend an adherence of 95% to achieve viral load suppression [5, 6]. Despite such recommended high adherence rates, several other studies have shown that a medication adherence rate of >  = 80% is sufficient to achieve viral load suppression [5, 7, 8]. The differences between these studies may relate to differences between antiretroviral drugs in so-called forgiveness for non-adherence. In any case, the importance of high ART adherence cannot be overstated in reducing HIV-associated morbidity, mortality, drug resistance, and transmission.

There is significant evidence that YPLHIV are the least adherent to ART as compared to other age groups, probably due to their formative stage of psychosocial and cognitive development in which they experience significant biological, psychological, and psychosocial transitions, rendered more difficult by the addition of an HIV diagnosis [3, 9]. Subsequently, sub-optimal ART adherence in YPLHIV leads to poor virological suppression rates and treatment outcomes.

Various digital health interventions have been implemented to improve ART adherence and viral load suppression in PLHIV, and some have proven to be effective [10]. Digital health technologies like real-time medication monitors (RTMM, i.e. pill box that records opening of the box) used in conjunction with SMS reminders and customised adherence feedback are promising tools for improving ART adherence and viral load suppression in YPLHIV. For example, a systematic review of digital health interventions in YPLHIV demonstrated that phone-based interventions might improve ART adherence and viral load suppression in adolescents [11].

Therefore, in this article, we describe the methodology of a randomised controlled trial to evaluate the effectiveness of a customised digital adherence tool (DAT) on ART adherence and viral load suppression in YPLHIV on ART in Blantyre, Malawi. We hypothesise that the RTMMs plus reminder text messages and tailored adherence feedback (RTMM-based DAT) could improve ART adherence and viral load suppression in YPLHIV on ART when compared to the standard of care which is intensive adherence counselling.

## Methods

The trial protocol has been written according to the SPIRIT reporting guidelines [12].

### Aim and objectives

#### Aim

The aim is to provide the evidence base for a digital adherence intervention that could improve treatment response and outcomes in YPLHIV on ART.

#### Objectives

The primary objective is to determine the efficacy of the customised DAT compared to the standard of care in improving ART adherence in YPLHIV.The secondary objective is to determine the efficacy of the customised DAT compared to the standard of care in improving viral load suppression in YPLHIV.

### Trial design

This will be a parallel open-label randomised controlled 2-arm trial in which YPLHIV will be randomised in a 1:1 ratio to the DAT and standard care (SOC) arms and followed up for 9 months. This design will enable us to evaluate the superiority of the intervention compared to the SOC. Figure 1 shows the flowchart of events.

**Fig. 1 Fig1:**
[figure not shown]
Flowchart of events

### Study setting

The study will occur in Blantyre, Malawi, in the ART clinics of the following primary health facilities: Bangwe, Ndirande, Limbe, Chilomoni, and South Lunzu. These facilities were chosen because they have the highest number of YPLHIV in Blantyre district.

### Eligibility criteria

The study population will be people living with HIV aged between 15 and 24 years (YPLHIV) on ART registered at the study sites. Participants will be YPLHIV who are non-adherent to ART, i.e. less than 80% of prescribed pill intake based on pharmacy refill counts.

To be included in the study, participants must be on first-line ART regimen (tenofovir/lamuvidine/dolutegravir) or (tenofovir/lamuvidine/efavirenz) according to local guidelines, must have had full disclosure of their HIV status, must be able to read and understand Chichewa or English, and must be competent in the use of mobile devices.

Exclusion criteria include hospitalisation at the time of study entry, prior participation in digital adherence health research, enrolment in other HIV-related studies, and treatment for a comorbidity that significantly increases the participants’ pill burden.

### Interventions

#### Standard of care

The standard of care involves routine ART clinic procedures and protocols as stipulated by the national guidelines [13]. These include intensive adherence counselling and targeted viral load testing after 3 months of optimal adherence for these clinic attendees for ART clinic attendees who are non-adherent and/or virologically non-suppressed or at risk of virological failure.

#### RTMM-based digital adherence tool

The RTMM is a pillbox developed by Wisepill™ containing a SIM card that sends data to a central server through the worldwide general packet radio service (GPRS) network. The pillbox can hold approximately 30 large pills or 60 small pills [14]. In the context of this study, the participants will store their ARV fixed combination tablets in the pillbox.

Data about openings will be immediately sent to and stored on a secure server. The data will include information about the opening time, the dispenser’s identification number, and battery and signal strength specifications. If medication is not taken within one hour of the prescribed time, the participant will receive a text message reminder. The messages will be neutral and unrelated to the HIV status of the recipients.

Participants in the intervention arm will also receive customised adherence feedback based on server-stored adherence data at every scheduled clinic visit. This feedback will be provided by a psychosocial counsellor or an ART nurse or clinician with the help of a research assistant. The feedback sessions will take into consideration the complex interaction of multiple factors unique to the demographic group of YLHIV. During these discussions, participants will go through the stages of precontemplation, contemplation, preparation, action, and evaluation according to the stages of change model. This approach has been adopted from a similar trial conducted by Sumari-de Boer et al. in Tanzania [15]. Participants will be asked about their opinion regarding their self-reported and pharmacy refill adherence since the previous visit (precontemplation), followed by being shown their adherence report from the RTMM server on which participants will be asked to reflect (contemplation). A discussion on possible barriers for adherence and next steps will then be undertaken and a target will be set for the next visit (preparation). After the feedback, participants will be expected to have increased intention to adhere, which should be followed by improved adherence (action). During the next visit, the same process will be repeated, including the evaluation of the preceding period. Lastly, since the intervention is an adherence aid, participants will undergo medical care as prescribed by ART clinic staff and according to Malawi HIV treatment guidelines. Therefore, participants enrolled in this study will not be barred from receiving any concomitant care.

### Outcomes

The primary outcome is the proportion adherent at 9 months, which is the percentage of prescribed drugs consumed as ascertained on the clinic visit. These will be determined at 1, 2,3, 6, and 9 months. Both self-reported adherence and pharmacy refill counts will be measured at each scheduled visit; these methods have been described in a similar trial by Sumari de Boer et al. [15]. A cut-off of >  = 95% of prescribed pill intake based on the Malawi National Guidelines will be used to classify participants as to whether they were adherent or non-adherent [13].

The secondary outcome is the proportion virologically suppressed at 9 months. A blood plasma sample will be collected for all study participants at baseline and at nine months for viral load testing using real-time polymerase chain reaction (rtPCR). Viral load suppression will be defined by a cut-off of < 200 copies/ml as this cut-off has been shown to have a zero transmission risk and is of public health importance in terms of epidemic control [16, 17].

Serum samples for viral load will be collected by the research assistant or clinic staff. We will follow standard care procedures in obtaining blood samples. These samples will then be sent to the Kamuzu University of Health Sciences Microbiology Laboratory for processing within 24 h.

### Participant timeline

Study procedures and timelines are also displayed in Table 1.

**Table 1 Tab1:**
[figure not shown]
SPIRIT figure for study procedures and events

*** t*_*1*_ = 1 month, *t*_*2*_ = 2 months, *t*_*3*_ = 3 months, *t*_*4*_ = 6 months, *t*_*5*_ = 9 months, *t*_*x*_ = 16 months

### Sample size

The sample size calculation is an estimation based on ART adherence. At endline, participants will be classified into 2 categories: adherent, and non-adherent based on pill count. The study intends to demonstrate a difference of 15% in adherent participants between the intervention arm (90%) and the control arm (75%). Since there is no recent published literature on baseline adherence levels in YPLHIV in Malawi, virological suppression data from the recent Malawi Population-based HIV Impact Assessment 2020–2021 [13] and an observational study on adherence and virological suppression conducted in the southern districts of Malawi [3] have been used as a proxy for ART adherence in this demographic, hence the 75% expected adherence proportion at endline for the SOC arm. With a power of 80% and *α* = 0.05, we will need 100 participants in each arm. Considering 20% loss-to-follow-up, the sample size needed is 120 participants in each arm. The R statistical package “pwr” version 1.3 was used to compute the sample size [18].

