### Statistical analysis

All analyses will be done using R [19]. Reporting will follow the CONSORT guidelines [20]. A flowchart will describe the inclusion and follow-up of participants by study arm. Baseline characteristics and outcomes will be described by the study arm with summary statistics for continuous variables and number and percentage for categorical variables.

The primary and secondary analyses for this study will be the comparison of adherence and viral load suppression proportions between study arms at month 9. A 2-proportion *z*-test will be utilised to test for statistical significance and 95% confidence intervals and *p*-values will be computed. The following analysis sets will be used for both the primary and secondary outcomes:Modified intention-to-treat (mITT): anyone found to be ineligible after randomisation will be excludedPer-protocol (PP) set: this set includes all participants who completed the study without a major protocol deviation

Furthermore, additional analyses of both the primary and secondary outcome will involve the use a logistic regression model adjusted for the pre-specified randomisation stratification factors (sex and age) [21] and important baseline characteristics if found to be unbalanced between study arms [22]. Furthermore, to determine the efficacy of the intervention over time, a multilevel logistic regression model will be utilised. A detailed statistical analysis plan will be submitted later. Lastly, missingness will be defined for important variables, and if appropriate, multiple imputation will be employed. Lastly, no interim analysis is planned, and subgroup analyses will be described in a detailed statistical plan.

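### Enrolling 120 per arm leaves 96, not the required 100, after 20% loss to follow-up; 125 per arm would be needed

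*Protocol article*

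**What the plan says.** The Sample size section of the protocol article bases the calculation on the proportion classed as adherent at the end of follow-up: 90% in the intervention arm and 75% under standard of care. It then gives two figures in consecutive sentences. The first is the number required: "With a power of 80% and *α* = 0.05, we will need 100 participants in each arm". The second is the number to enrol: "Considering 20% loss-to-follow-up, the sample size needed is 120 participants in each arm". The calculation is credited to version 1.3 of the R package pwr.

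Under Trial design the allocation is 1:1. Under Statistical analysis the planned comparison at month 9 is given as follows: "A 2-proportion *z*-test will be utilised to test for statistical significance". The article gives no other retention assumption and no larger enrolment target.

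**The concern.** The 120 per arm appears to come from adding 20% to the number required, when it should come from dividing that number by the fraction expected to remain. The two operations differ because the loss applies to everyone enrolled, including the extra participants brought in to cover it. If so, the four design figures (80% power, 100 required, 20% loss, 120 enrolled) do not agree. At the loss rate the protocol itself plans for, the trial would finish with fewer participants than it says it needs, and its 80% power would not be met by the test it plans to use. The enrolment target is a core design figure against which recruitment and the final report will be judged.

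**Working it through.** **Inputs.** All are from the Sample size section unless noted.
- Proportions adherent: p1 = 0.90, p2 = 0.75, difference 0.15.
- Power 80%, α = 0.05. Sidedness is not stated. Two-sided is assumed because it reproduces the stated 100; one-sided gives 79.
- Allocation 1:1 (Trial design).
- Test: two-proportion z-test (Statistical analysis).
- Loss to follow-up d = 0.20; enrolment 120 per arm.

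**Step 1: reproduce the 100.** The pooled z-test formula is

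n = [z(0.975) × √(2·p̄·(1 − p̄)) + z(0.80) × √(p1(1 − p1) + p2(1 − p2))]² / (p1 − p2)²

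with p̄ = (0.90 + 0.75)/2 = 0.825.
- √(2 × 0.825 × 0.175) = √0.28875 = 0.5374
- √(0.09 + 0.1875) = √0.2775 = 0.5268
- n = (1.960 × 0.5374 + 0.8416 × 0.5268)² / 0.15² = 99.5, rounded up to 100 per arm.

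This matches the stated figure exactly.

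The two-proportion routine in pwr uses the arcsine effect size h = 2·arcsin√0.90 − 2·arcsin√0.75 = 0.4037. It gives n = 2 × [(1.960 + 0.8416)/0.4037]² = 96.3, rounded up to 97.

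**Step 2: apply the 20% loss.**
- Number to enrol so that 100 remain: 100/(1 − 0.20) = 125 per arm.
- Stated number: 100 × (1 + 0.20) = 120 per arm.
- Shortfall: 5 per arm, 10 in total (250 against 240), or 4% of 250.

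**Step 3: what 120 delivers.**
- Remaining after 20% loss: 120 × 0.80 = 96 per arm, 4 below 100.
- Largest loss that still leaves 100: 1 − 100/120 = 16.7%.

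**Step 4: power for 90% against 75%, two-sided α = 0.05.**

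| Evaluable per arm | Pooled z-test | Arcsine |
|---|---|---|
| 96 | 78.5% | 79.9% |
| 97 | 79.0% | 80.3% |
| 100 | 80.2% | 81.4% |

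For the pooled test at 96, power is Φ[(0.15 × √96 − 1.960 × 0.5374)/0.5268] = Φ(0.791) = 78.5%. For the arcsine method at 96, it is Φ(0.4037 × √48 − 1.960) = Φ(0.837) = 79.9%.

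**The case against.** The best defence rests on the cited software. If the calculation was done with the arcsine method of pwr, the unrounded requirement is 96.3 per arm, and 96.3/0.80 = 120.4. On that basis 120 is almost exactly right. The 96 who remain after 20% loss give 79.9% power, which rounds to the stated 80%. Even by the pooled z-test, going from 100 to 96 costs only about 1.6 points of power, and only if loss reaches the full 20%. The Data collection methods section describes active tracing by phone and home visit, which may keep loss lower. Uncertainty about the 75% control proportion, which the protocol takes from viral suppression data as a proxy, probably matters more for power than five enrolments per arm.

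The points about size stand: the consequence is small and depends on the loss actually occurring. The defence of the arithmetic does not stand. The protocol gives the number required as 100, not 96 or 97, and 100 is what the pooled formula for the planned test returns. Rounding the arcsine result up to whole participants gives 97, and 97/0.80 = 121.25, which means 122 per arm, still not 120. If the arcsine route was the one used, then the stated 100 is the figure that needs correcting. Tracing does not settle the matter either, because 20% is the allowance the protocol chose with that tracing in its plan.

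**Conclusion.** The enrolment target is wrong on the protocol's own figures. A requirement of 100 per arm with 20% loss calls for 125 enrolled per arm, and 120 leaves 96. The shortfall is 5 enrolled per arm (10 overall). If loss reaches 20%, power is 78.5% by the pooled z-test or 79.9% by the arcsine method, against the 80% stated. If loss stays at or below 16.7%, the required 100 are kept.

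The enrolment arithmetic rests only on the stated 100, 20% and 120. The power figures also rest on 75% against 90%, two-sided α = 0.05 and equal arms; whether 75% and 90% are realistic was not examined here. The error does not threaten the trial, but it should be corrected. The margin is thin, because the modified intention-to-treat set also drops participants found ineligible after randomisation and the per-protocol set will be smaller again.

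**What to change.** Choose one of the following and amend the Sample size section to match.

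1. **Keep 120 per arm and restate the allowance.** Say that 120 per arm keeps 100 evaluable with up to 16.7% loss, and that 20% loss leaves 96 per arm, with power of about 78.5% by the pooled z-test (79.9% by the arcsine method) for 75% against 90%. Name the method beside any power figure, since the paragraph credits pwr while the planned test is a z-test. This costs one sentence and no extra participants, and it is the only option left if recruitment has closed.
2. **Raise the target to 125 per arm (250 in total).** This keeps both the 20% loss and the 100 evaluable. It costs 10 more participants.
3. **If the arcsine result was in fact the basis, correct the requirement itself.** State 97 evaluable and 122 enrolled per arm (244 in total). This costs 4 more participants than now planned.

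In each case, state that the test is two-sided. Given the small effect on power, the first option is enough.

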### Recruitment

Since participants will be recruited from ART clinics, research assistants in addition to, ART clinic personnel and research assistants will be trained on the protocol and will be responsible for identifying eligible clients. In addition, posters and flyers will be displayed in ART clinics to raise awareness of the study.

### Allocation to study arms

For allocation to study arms, stratified block randomisation with variable block sizes will be employed. Allocation cards will be printed and stored in envelopes that will be kept in secure lockable cabinets at the recruitment sites. During the screening/first visit, the research assistant will assign and enrol study participants. The participants’ gender and age will be stratifying factors. The data manager will be responsible for creating allocation cards, while the research assistants will assign participants to each study arm.

Furthermore, it will not be feasible to blind participants and site investigators to arm allocation due to the nature of the intervention. However, for the assessment of the secondary endpoint, laboratory staff processing viral loads will be blinded to arm allocation. Furthermore, the trial statistician will be blinded to study arms when assessing the primary and secondary outcomes.

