### Data collection methods

A research assistant will screen for eligibility, solicit consent, and enrol participants. The research assistant will hand an informed consent form to a potential participant in their preferred language and collect baseline characteristics and information on outcomes when applicable.

To minimise loss to follow-up, at enrolment, a geolocation of participants’ place of residence using the ePAL android app, a high-resolution mapping system validated in Blantyre will be used should participants consent. We will also record up to 3 contact phone numbers of the participant and their nominated friends and relatives. Should a participant miss a study visit, we will contact them by phone or by visiting them at home to encourage them to attend the study visit before the expiry of the prescribed visit window.

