### Data management

Standardised, pre-tested questionnaires will collect data from participants at every visit. The electronic data collection tools will be designed using REDCap. All paper records will be kept in a locked space and will only be accessible to approved study staff. Furthermore, for the real-time medication monitoring, anonymised data will be stored on a secure server.

Routine data quality assurance processes will be conducted from time to time. Queries will be raised in the database to resolve data recording inconsistencies. In addition, a random sample of individual participant records in the database will be cross-checked with source documents for the correctness of data entry procedures during quality assurance monitoring.

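### Allocation envelopes are held at the clinics and drawn by the research assistant who also screens and enrols, and the sex-and-age strata are not reconciled with five separate envelope stores

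*Protocol article*

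**What the plan says.** The section on allocation to study arms states that "stratified block randomisation with variable block sizes will be employed" and that "gender and age will be stratifying factors". On custody it says: "Allocation cards will be printed and stored in envelopes that will be kept in secure lockable cabinets at the recruitment sites". The data manager makes the cards. At the screening or first visit, "the research assistant will assign and enrol study participants".

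The data collection section gives the same role the steps before assignment: "A research assistant will screen for eligibility, solicit consent, and enrol participants". It also has this role collect baseline data and outcome information. Under the description of the digital tool, a research assistant helps the clinic staff deliver adherence feedback in the intervention arm. Participants and site investigators are not blinded. Blinding is stated only for the laboratory staff who process viral loads and for the trial statistician.

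Recruitment takes place at five clinics: "Bangwe, Ndirande, Limbe, Chilomoni, and South Lunzu". The statistical analysis section names sex and age as the stratification factors in the additional logistic model and allows further adjustment for notable baseline imbalances. On data management the article says: "The electronic data collection tools will be designed using REDCap".

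**The concern.** Allocation concealment means that whoever decides on entry cannot learn or predict the next arm. Here that role also works the envelopes, on the same premises. A locked cabinet keeps outsiders away, but it is no barrier to the person who has to take the next envelope from it. If the next arm is known or guessed, entry can be hastened, delayed or refused for a particular young person. Two eligibility criteria leave room for this: being able to handle a mobile device, and not being treated for another illness that adds materially to the pill burden. Adjustment for sex and age would not remove a selection effect of this kind. It would also come on top of a primary outcome, the pill count, that the article's own limitations describe as open to manipulation and observer bias.

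A second and smaller matter is how the strata fit the physical system. The declared strata are sex and age, but the cards sit in separate stores at five clinics. The article does not say whether each clinic has its own sequences. That decides whether site is in fact a stratification factor and belongs in the model that adjusts for such factors.

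**Working it through.** **1. The plan's own figure, used only as an input.** The sample size section gives 100 per arm for 90% against 75%, with 80% power and alpha 0.05. The pooled two-sided formula reproduces it: [1.96 × √(2 × 0.825 × 0.175) + 0.8416 × √(0.75 × 0.25 + 0.90 × 0.10)]² / 0.15² = (1.053 + 0.443)² / 0.0225 ≈ 99.5, so 100. The plan's 120 per arm gives 2 × 120 = 240 in total. This point disputes no number in the plan.

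**2. Roles side by side.**

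| Step | Who | Section |
|---|---|---|
| Preparing the cards | Data manager | Allocation to study arms |
| Keeping the envelopes | Cabinets at the clinics; key-holder not stated | Allocation to study arms |
| Screening, consent, enrolment | Research assistant | Data collection methods |
| Assigning the arm | Research assistant | Allocation to study arms |
| Helping with intervention feedback | Research assistant | Interventions |
| Collecting outcome information | Research assistant | Data collection methods |

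The sequence is produced away from the recruiter, which is a real safeguard. From the cabinet onward, every step falls to the recruiting role, and no stated step requires eligibility and consent to be recorded before the envelope is opened.

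**3. How predictable blocks could be.** In a balanced block of size 2m, the assignments fixed by those before them form the block's final run of one arm. The expected length of that run is 2m/(m + 1), so the determined fraction is 1/(m + 1): 1/2 for size 2, 1/3 for size 4, 1/4 for size 6 and 1/5 for size 8. The article does not give its block sizes, so mixtures were assumed and simulated (4,000 runs, cells of 12 and of 60):

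- Fixed blocks of 4: 33%
- Sizes 4 and 6: 25% to 28%
- Sizes 2, 4 and 6: 30% to 31%
- Sizes 4, 6 and 8: 21% to 24%

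These are upper guides. They require the recruiter to know the size of the block in use and to have seen every earlier assignment in it. The second condition is met naturally only if each clinic runs its own sequences.

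**4. Strata and sites.** The inputs are 240 participants, 5 sites and 2 sexes, with 2 or 3 age bands assumed.

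- Sex × age: 2 × 2 = 4 cells of 60, or 2 × 3 = 6 cells of 40.
- Site × sex × age: 5 × 2 × 2 = 20 cells of 12, or 5 × 2 × 3 = 30 cells of 8.

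The simulation used the three variable-block mixtures above, with sites and strata equal in expectation. Each site then has about 240/5 = 48 participants. Entries are absolute differences in numbers between arms, given as the range of means across scenarios, with 95th percentiles in brackets.

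| Scheme | Whole trial | Largest difference at any one site |
|---|---|---|
| One trial-wide sequence per sex-by-age cell | 1.4 to 2.1 (4 to 6) | 9.4 to 9.5 (16) |
| Separate sequences per site | 3.4 to 4.8 (8 to 12) | 3.0 to 4.3 (5 to 7) |

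Both schemes keep the arms close overall. They differ in balance within sites and in whether site is a stratum. The first needs a central draw, because successive participants in a cell may present at different clinics. Separate paper stores cannot supply one sequence in order.

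**The case against.** The strongest reply is that a recruiter opening an envelope prepared by someone else is how envelope randomisation ordinarily works. The article does state safeguards: variable block sizes, lockable cabinets and cards made by a different role. It does not say that the research assistant holds the key or knows the block sizes. The main entry criterion is numeric (refill adherence below 80%), and clinic personnel also help to identify candidates. All of this stands. It lowers the risk but does not separate the recruiter from the envelopes.

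The article also does not describe the envelopes as sealed, opaque or numbered. A condensed article commonly leaves that to the full protocol, so it is no part of this point.

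A reader might infer that sex-by-age blocks cannot operate at all under this arrangement. The text does not support that. It never says there is a single trial-wide list, and envelope sets kept separately at each clinic fit its wording and are feasible.

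A reader might also infer that site is neither balanced nor adjusted for. That goes too far. Per-site sets would balance arms within sites, and the adjusted model may take in baseline characteristics found to be unbalanced, which could include site. Leaving site out of the strata is a legitimate choice. With sound concealment it leaves chance imbalance and does not bias the comparison, and the article reports no differences between clinics in adherence.

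**Conclusion.** The point holds as a weakness in the stated allocation method. In an open-label trial, one site-based role screens, consents, enrols, assigns and collects outcome information, and draws from envelopes held at its own clinic. A less exposed method is within reach. This does not show that allocation will be foreseen or that the result will be biased, and the document offers no basis for a bias in percentage points. The 21% to 31% range describes predictability only, and rests on assumed block sizes and on the recruiter knowing the one in use.

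The secondary point is one of reconciliation. The sections on study setting, allocation and statistical analysis leave open whether sequences are trial-wide or per site. Either is statistically workable, but only per-site sequences suit five separate cabinets, and those make site a stratum in practice. The cell counts assume two or three age bands and equal expected recruitment across sites and strata.

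**What to change.** - Release each allocation centrally through REDCap, which is already planned for data collection. Let the system show the arm only after eligibility, consent and baseline data have been saved.
- Keep the list away from site staff, and do not disclose the block sizes to them. Central release removes access to the next card but does not stop guessing from past assignments, so variable blocks still matter.
- Keep envelopes at the clinics only as backup for connection failure.
- State whether the sequences are trial-wide or per site. If they are per site, declare site as a stratum alongside sex and age, and add it to the adjusted logistic model.

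The cost is a short set-up, brief training and the need for connectivity at enrolment. Declaring site raises the number of cells to 20 or 30 under the assumed age bands, which the simulated imbalances show is manageable. The sample size does not change.
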